### 2.3. Participants

All under-4 children and their mothers/caretakers, resident in the selected hamlets, will be considered eligible and invited to participate. This age group was selected because children are expected to have limited mobility, to receive higher parental attention and to have their exposure to contaminated environments more controllable than school aged children. Children will be subject to exclusion whenever having recently received blood transfusions, report adverse reactions to albendazole and/or to praziquantel, and when their caretakers do not commit to completing both the evaluation and the educational moments of the study. Only children with pre-intervention evaluation will be allocated to the Randomized Controlled Trial (RCT).

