### 2.7. Sample Processing

Stool, urine and blood will be analyzed parasitologically. Blood protozoa (*Plasmodium falciparum* and *Plasmodium vivax*) will be determined by the Rapid diagnostic test (*SD BIOLINE* Malaria Ag P.f/P.v (HRP-2/pLDH, Standard Diagnostics, INC, Suwon City, Korea))*,* intestinal helminths (*Ascaris lumbricoides, Trichuris trichiura*, *Hymenolepis nana* and *Strongyloide stercoralis*) determined through fecal smear according to the Katokatz technique, intestinal protozoa (*Giardia lamblia* and *Entamoeba hystolitica/dispar*) evaluated through fecal centrifugal-sedimentation (using Parasitrap® System, Biosepar, Mühldorf, Germany) and urogenital helminth (*Schistosoma haematobium*) determined by urine filtration [48,49]. Biochemical analyses will comprise quantifying hemoglobin directly from peripheral blood (using Hemocue ® Hb 301 System, Angelholm, Sweden), serum ferritin, C-reactive protein and zinc through kits from Quimica Clínica Aplicada (Quimica Clínica Aplicada S.A., Tarragona, Spain) and an automated analyzer (BT1500, Biotecnica Instruments S.p.A, Rome, Italy), serum retinol through high-performance liquid chromatography with a protodiode-array detection, and vitamin B12 and folic acid by chemiluminescence immunoassay (using VITROS® Immunodiagnostic kits, Ortho Clinical Diagnostics, Inc. Bridgend, UK) [50,51,52,53]. Molecular analysis will include DNA extraction (by Chelex method), screening for sickle cell trait and disease (by PCR) and G6PD deficiency (by rtPCR) [54,55]. Malaria diagnosis will take place on site, and stool/urine samples will be analyzed within 24/48 h of collection (depending on the day of the week). The laboratory analyses will be performed by trained technicians and 25% of tests subject to confirmation by experienced laboratory supervisors.

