## 4. Data Collection

### Educational Interventions

Caretakers participating in the intervention arms will have a monitoring file (consisting of six structured questionnaires (one for each monthly visit), applied by the technician to document behavioral alterations at every counselling visit and to record attendance to the community group sessions. Those educational interventions will be intercalated with cross-sectional evaluations. Those moments will have the same design as the baseline assessment, occurring respectively six and twelve months after the beginning of the study.

Data on the primary and secondary outcomes, which will be collected only in the follow up moments, aim at evaluating the impact of interventions. Considering that interventions are expected to influence either health and behavioral aspects, impact indicators are expected to provide information on changes in their frequency, and potential associations. On the other hand, data on the process indicators, which will be collected throughout the study, aim at assisting the evaluation of the quality and success of intervention’s delivery process. Thus, data regarding the provision, utilization and coverage aspects of the delivery process are expected to facilitate attributing the changes in primary and secondary outcomes to the intervention, by demonstrating that the intervention was of sufficient magnitude and occurred in a temporal sequence. Specifically, (1) provision indicators are expected to inform about the quality of provider’s training and performance, and if the requirements for provider’s optimal performance was delivered to them; (2) utilization indicators are expected to inform about the quality of receiver’s sensibilization, their receptivity to interventional activities, acquired knowledge and alterations of inadequate behaviors toward children; and (3) coverage indicators aim at providing information regarding the quality of the interventional activities, such as the adherence to them.

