### 5.2. Baseline Assessment Eevaluations

The nutritional quality of children’s diets (24–36 months) will be determined in accordance with the Children’s Individual Dietary Diversity Score Indicator (IDDS) [69,70]. The prevalence of malnutrition in children will be calculated by WHO Anthro software (version 3.2.2). The chi-square test will be used to compare proportions, in addition to calculating the attributable fractions.

Pre-and post-intervention and intervention versus control arms evaluations.

Primary and secondary impact indicators will be evaluated between the baseline and the follow ups (for each study sample), and between the intervention and control arms. Outcomes will be compared analyzing for variance in the continuous variables and logistical regression for the categorical variables. Adequacy and plausibility arguments will be used, by analyzing the process indicators (described in Table 2) in accordance with the conceptual maps. Relative risk will be calculated in order to compare the cumulative incidence of anemia among the intervention and control arms.

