1. Primary outcomes 1.1 Impact on health - Variation of hemoglobin levels; - Anemia prevalence reduction. 2. Secondary outcomes 2.1 Impact on Health - Iron deficiency anaemia reduction; - Micronutrient deficiencies (iron, folate, vitamins A and B12, zinc and vitamin E serum levels); - Prevalence reduction, intensity, incidence and reinfections rates of STH, *P. falciparum* and *S. haematobium*; - Prevalence reduction of Stunting (height-for-age) and wasting (weight-for-height). 2.2 Impact on Behavior - Exclusive breastfeeding (0–5 months) and continued breastfeeding (12–15 months) [68]; - Increase of Minimum dietary diversity prevalence (6–23 months) [68]; - Increase of Minimum Meal Frequency prevalence [68]; - Increase of iron and vitamin A rich foods consumption; - Reduction of morbidity from diarrhea (reported).	1. Acquired knowledge - Theoretical test scores (evaluation of knowledge); - Practical test scores (evaluation of counseling performance); - Self-counseling efficacy evaluation. 2. Counseling performance - Number of families dropping outs from evaluation moments per technician; - Number of families successfully visited for counseling by each technician; - Number of notified participants present in each community groups per technician; - Number of scheduled visits held successfully per technician.	1. Acquired knowledge of receivers -Theoretical test scores; - Practical test scores (participation in community groups); - Self-evaluation at mother-to-child care. 2. Participatory level of receivers (adherence) - N° of attendances to evaluation moments; - N° of scheduled visits (both in person and by telephone call) held successfully; - N° of scheduled visits that had to be redials due to absence or unavailability; - Mood state of the receiver between visits; - N° of attendances to communitarian group. 3. Household environment evaluation (observation) - N° of household hand washing mechanisms; - N° of communitarian latrines around the house; - Cleaning conditions classification of household latrines (if existent); - Cleaning conditions classification of the backyard; - Presence of pets loose in the yard and stool. 4. Mother-to-children care practices - Children using bednets; - Children sidewalks; - Children with clean nails.	1. Services provided at evaluation moments - N° of hospital-based consultation held for parasite treatment; - N° of domiciliary-based consultation held for parasite treatment; - N° of hospital-based consultation held for sickle-cell follow up; - N° of children referred to the emergencies with severe anemia, severe malnutrition and non-malarial fever who reported to have been followed. 2.Participatory level of receivers (adherence) - Proportion of child-caretaker pair present in all evaluation moments; - Proportion of child-caretaker pair presenting in all counseling moments; - Proportion of caretakers participating in all community groups; - N° of notified child-mother pair failing the hospital-based consultations for parasite treatment or sickle-cell follow up; - N° of child-mother pair failing to picking up the sickle-cell drugs.

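### Exclusive breastfeeding at 0–5 months cannot be usefully compared between arms at the 6- and 12-month waves, and two components listed in Table 2 have no named measurement

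*Protocol article*

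**What the plan says.** **Outcome.** Table 2 gives "Exclusive breastfeeding (0–5 months) and continued breastfeeding (12–15 months") among the secondary outcomes on behaviour.

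**Who is in the trial.** Section 2.3 sets entry at under 4 years ("All under-4 children and their mothers/caretakers, resident in the selected hamlets, will be considered eligible and invited to participate") and then restricts the trial: "Only children with pre-intervention evaluation will be allocated to the Randomized Controlled Trial (RCT"). Section 3.6 describes finding the enrolled families again through the surveillance system's household identifiers and telephone numbers. It describes no enrolment of new births.

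**When outcomes are taken.** Section 4 confines primary and secondary outcome data to the follow-up evaluations, "occurring respectively six and twelve months after the beginning of the study". It calls these evaluations cross-sectional and says they are built like the baseline. Behaviour is also recorded monthly, but: "Caretakers participating in the intervention arms will have a monitoring file".

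**Comparisons.** Section 5.2 plans to compare the impact indicators between baseline and follow-up, and between intervention and control arms.

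**Laboratory measures.** Table 2 lists "Micronutrient deficiencies (iron, folate, vitamins A and B12, zinc and vitamin E serum levels"), and also the intensity of soil-transmitted helminths, *P. falciparum* and *S. haematobium*. Section 2.7 itemises the analytes and methods. For malaria, the blood parasites "will be determined by the Rapid diagnostic test".

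**The concern.** An outcome restricted to the first six months of life needs children of that age when it is measured. A cohort closed at baseline and seen again after 6 and 12 months has aged out of the window. Both comparisons in section 5.2 would then have a follow-up cell that is empty or nearly so.

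This matters beyond bookkeeping. Breastfeeding is the first target of the nutrition package in Table 1, and section 1.2 makes less inadequate breastfeeding a step in the causal chain of the nutrition arm. If the gap is noticed only at analysis, the tempting substitute is the counselling record, which has no control group. Control-arm information on early feeding becomes harder to recover with each month after the 6-month wave.

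The vitamin E and *P. falciparum* intensity entries raise a smaller point of the same kind: each is promised as an outcome, and the methods section does not say how it will be obtained.

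**Working it through.** The article gives no figure on this point, so there is none to reproduce. The check is age arithmetic plus a cross-reading of Table 2 against section 2.7.

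**Inputs.** Age at baseline *a* runs from 0 to under 48 months (section 2.3). Follow-up is at 6 and 12 months (section 4). The windows are 0–5, 12–15 and 6–23 months (Table 2). Assumption: ages are evenly spread, one forty-eighth of the children per month of age.

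**Step 1: waves 6 and 12 months after each child's own baseline.** Age at a wave = *a* + 6 or *a* + 12, so the youngest possible child is 6 months old at the first wave and 12 months old at the second.

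| Window | Baseline | 6 months | 12 months |
|---|---|---|---|
| 0–5 months | 6/48 = 12.5% | 0/48 | 0/48 |
| 12–15 months | 4/48 = 8.3% | 4/48 | 4/48 |
| 6–23 months | 18/48 = 37.5% | 18/48 | 12/48 = 25% |

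The two zeros do not depend on the even spread of ages; they follow from *a* ≥ 0. The other cells do depend on it.

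**Step 2: waves timed from study start.** Section 4 counts from the beginning of the study, so a child enrolled *t* months after the start is aged *a* + 6 − *t* at the first wave, and is under 6 months only if *a* < *t*. Suppose enrolment is even over *W* months and the first wave falls at month 6. The share of the cohort still in the window is then the average of *t*/48 over 0 to *W*, which is *W*/96:

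- *W* = 0.5: 0.5%
- *W* = 1: 1.0%
- *W* = 2: 2.1%
- *W* = 3: 3.1%

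As a share of the infants who were 0–5 months at baseline, this is *W*/12, or 4.2% to 25%. At the second wave the youngest child is 12 − *W* months old, so at least 9 months, and the window is empty.

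*W* is an assumption. Section 2.5 gives up to 45 children a day and the article gives no total. For 500 to 3,000 children that is 500/45 = 11 to 3,000/45 = 67 field days, roughly half a month to three months at five days a week.

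**Step 3: measurements.** Table 2 names six micronutrients. Section 2.7 supplies a counterpart for five: ferritin for iron, folic acid, retinol for vitamin A, vitamin B12 and zinc. It has none for vitamin E. For intensity, the stool smear and urine filtration are egg-based methods that can serve the helminths. For *P. falciparum* there is only the rapid antigen test. The molecular work covers sickle cell and G6PD deficiency. No parasite count or quantitative PCR is named.

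**The case against.** **The waves may be fresh censuses.** Section 4 calls them cross-sectional and modelled on the baseline, and the baseline was a house-to-house census. A repeat census would reach newborns. This is the best argument on the other side, and it shows that the text is not fully consistent. It does not rescue the outcome as written: section 2.3 limits the trial to children with a baseline evaluation, and section 3.6 relocates known families. Even on this reading the passages need reconciling.

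**The questionnaire may already ask how long exclusive breastfeeding lasted.** Section 2.6 says it covers breastfeeding and complementary feeding, and the instrument is not shown. That is possible, but Table 2 defines the outcome by age at 0–5 months, not by duration recalled later.

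**The full protocol may name more assays.** It may. However, section 2.7 lists analytes one by one with their methods, so the mismatch with Table 2 lies inside the article. The infection line is compressed, and its author may never have meant intensity to apply to malaria; if so, the table should say so.

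**Stronger readings that the documents do not support.**
- A reader might infer that the trial cannot show any change in breastfeeding. Continued breastfeeding at 12–15 months stays observable in all arms, at about 8.3% of the cohort per wave.
- A reader might infer that minimum dietary diversity (6–23 months) loses most of the cohort through ageing. The counts are 18, 18 and 12 of 48. Most children are outside that window from the start because the indicator is openly age-specific, which is not an error.
- A reader might object to the sentence "The nutritional quality of children’s diets (24–36 months) will be determined in accordance with" a dietary diversity score. It stands with the baseline assessment, and Table 2 does not list that score as an outcome.
- A reader might count three whole outcomes as lost. Each of the three items is one component of a composite line, and the other components stand.

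**Conclusion.** The point holds in a limited form. As written, exclusive breastfeeding at 0–5 months gives no useful comparison between arms: none of the cohort is in the window if each child is seen 6 and 12 months after its own baseline. If the waves are timed from study start, a few percent at most (0.5% to 3.1% for an assumed enrolment period of 0.5 to 3 months) remain at the first wave, and none at the second. This rests on reading section 2.3 as a closed cohort, which sections 2.3 and 3.6 together favour. The percentages also assume evenly spread ages.

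Serum vitamin E and *P. falciparum* intensity are mismatches between Table 2 and section 2.7, and smaller matters. Hemoglobin and anemia prevalence, the primary outcomes, are unaffected, as are the diet indicators. The change should be made before the 6-month wave, but the trial does not stand or fall on it.

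**What to change.** 1. **Redefine the breastfeeding item** in Table 2 as exclusive breastfeeding maintained to 6 months, or age at first other food. Ask it at the 6-month wave, with identical wording in all three arms, for infants under 6 months at baseline. These infants will then be 6 to 11 months old, so caretakers look back less than six months past the sixth month of life. Keep continued breastfeeding at 12–15 months as it is.
2. **Reconcile section 2.3 with section 4**: state whether infants born after baseline are included at follow-up. If they are, amend section 2.3 and describe their enumeration in the same way for all arms, since they would be recruited after allocation is known in an unblinded trial.
3. **Reconcile Table 2 with section 2.7**: delete serum vitamin E and *P. falciparum* intensity, or name the method for each.
4. **Do not use the monitoring files** for a between-arm comparison of exclusive breastfeeding, since they have no control counterpart.

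The cost is a questionnaire item and changes of wording, plus an assay only if the sponsor chooses to keep the two laboratory items. The downside is some error in caretaker recall of the breastfeeding item. Treatment and sample size do not change.

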### 2.2. Study Design

#### Baseline Assessment (Pre-Intervention Evaluation)

There were two qualitative pilot studies: (1) to characterize mother-to-child nutritional practices (as a basis to structure the questionnaire) and (2) to design a locally adequate Food Photography Atlas (FPA) for children U5 (for the 24 h recall evaluation). The first study was conducted between August and September of 2014 and enrolled 808 children aging 0–59 months and their caretakers in a two-stage cluster sampling strategy. Using a Portuguese translated questionnaire, adapted from ProPAN 14, we collected data on children’s breastfeeding, feeding practices and detailed food consumption in the previous 24 h [44]. As a result, data regarding the commonly consumed food was collected and a preliminary FPA S was produced. Following this, the second study, aiming at validating the previously mentioned FPA and to allow for the collection of age and context-specific food portion and nutrient ingestion among preschool children from the Bengo province, was conducted between February and March 2015. This was a convenient cross-sectional study that enrolled 75 primary caretaker residents in the Mabungo and Riceno hamlets within CISA’s study area. In sum, dishes were prepared according to local recipes, food photographs were produced, tested and selected, portion sizes were estimated and validated, and the reproducibility of this tool was evaluated. These results are being published elsewhere.

Using these tools, a pre-intervention evaluation, aiming to characterize the study population regarding anemia and its etiologic profile (by specific age groups (children aged under 6 months, between 6 and 23 months and between 24 and 36 months), will be performed.

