### 3.6. Recruitment and Promotion of Adherence

To relocate families, field technicians will perform a house-to-house invitation strategy, using Dande’s HDSS household identification system, reference points and family phone numbers. To increase adherence and promote participant retention, the hamlet coordinators and/or traditional authorities will be invited to be present at all phases of the study. Furthermore, incentive kits will be distributed to all children during the follow up moments, namely a nutritional kit (water and yogurt) and a WASH/Malaria kit (soap and lye).

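### At month 12 the 6–23 month dietary diversity indicator holds only children aged 12–23 months, so its planned change from baseline can reflect age alone

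*Protocol article*

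**What the plan says.** The outcome is in Table 2 of the protocol article, under secondary outcomes, impact on behavior: "Increase of Minimum dietary diversity prevalence (6–23 months". It is worded as a rise in a prevalence and tied to a fixed age window.

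Four other places decide who is in that window at each visit.

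- Section 2.3 sets the entry age: "All under-4 children and their mothers/caretakers, resident in the selected hamlets, will be considered eligible and invited to participate". It also closes the cohort: "Only children with pre-intervention evaluation will be allocated to the Randomized Controlled Trial (RCT".
- Section 3.6 describes finding the same families again: "To relocate families, field technicians will perform a house-to-house invitation strategy".
- Section 4 places the follow-ups as "occurring respectively six and twelve months after the beginning of the study", with the same design as the baseline assessment.
- Section 5.2 states the comparison: "Primary and secondary impact indicators will be evaluated between the baseline and the follow ups (for each study sample", and, in the same sentence, between intervention and control arms.

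The recall tool is not the limit. Section 2.2 describes a "Food Photography Atlas (FPA) for children U5 (for the 24 h recall evaluation", and the oldest entrant (47 months) is 59 months old at month 12.

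**The concern.** A fixed age window applied to a closed cohort selects different children at each visit. A child aged 15 months at entry is scored at baseline and has left the window a year later. A child aged 3 months at entry is not scored at baseline but is scored at month 12. The youngest part of the window, 6–11 months, cannot be refilled, because nobody enters after baseline. The baseline-to-month-12 comparison in Section 5.2 therefore sets a group aged 6–23 months against a group aged 12–23 months. If the share of children meeting the indicator differs between 6–11 and 12–23 months, the figure changes in every arm even when no family has changed its feeding.

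Dietary diversity is a named step in the nutrition arm's causal chain (Section 1.2, hypothesis 1). Sections 4 and 6 also rely on intermediate evidence to attribute changes in outcome to the intervention. A within-arm rise that is partly or wholly due to age would be read as support for that chain.

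**Working it through.** The plan gives no figure for this indicator to reproduce, so the check counts monthly age bands.

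**Inputs.** Entry ages are 0–47 completed months, 48 bands (Section 2.3). The window is 6–23 months, 18 bands (Table 2). Visits are at 0, 6 and 12 months (Section 4). There is no entry after baseline (Section 2.3). The age distribution is not given. Even ages are assumed first, then a linear gradient with the oldest band 0.6 to 1.5 times as dense as the youngest. No loss to follow-up is assumed.

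**Who is scored.** A child of entry age *a* is scored at visit *w* if 6 ≤ *a* + *w* ≤ 23.

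| Visit | Entry ages scored (months) | Share, even ages | Part of scored group aged 6–11 months |
|---|---|---|---|
| Baseline | 6–23 | 18/48 = 37.5% | 6/18 = 1/3 |
| Month 6 | 0–17 | 18/48 = 37.5% | 6/18 = 1/3 |
| Month 12 | 0–11 | 12/48 = 25% | 0 |

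The zero at month 12 does not depend on the age distribution. The 25% does: it is 21–30% under the gradients. If entry stopped near 36 months, where the baseline age groups in Section 2.2 end, it is 32–33% with even ages and 28–39% with the gradients.

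**Overlap between baseline and month 12.** Only entrants aged 6–11 months are scored at both visits: 6/48. So 12 of the 18 baseline bands (two thirds) have left the window, and 6 of the 12 month-12 bands (half) were not scored at baseline.

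**Change from age alone.** Let p₁ be the prevalence at 6–11 months and p₂ at 12–23 months, both unchanged over the year.

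- Baseline: (6p₁ + 12p₂)/18
- Month 12: p₂
- Change: p₂ − (6p₁ + 12p₂)/18 = (p₂ − p₁)/3

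| p₂ − p₁ (assumed) | Change with no effect |
|---|---|
| −10 points | −3.3 points |
| 0 | 0 |
| +10 points | +3.3 points |
| +20 points | +6.7 points |
| +30 points | +10.0 points |

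More generally the change is *s*(p₂ − p₁), where *s* is the 6–11 month share of the baseline scored group. Across the gradients and both upper ages, *s* runs from 0.31 to 0.36, so one third is a stable multiplier. The gap p₂ − p₁ is not in the documents.

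**Month 6.** Under even ages the 6–11 month share is one third at both visits, so the same calculation gives no drift. Under the gradients the two shares differ by at most about 0.002.

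**The case against.** **Section 5.2 also compares arms.** This is the strongest point and it stands. All arms age equally, so ageing does not by itself bias the difference between them. A reader might infer that the trial's test of the education effect on diet is confounded by age; the documents do not support that. What the randomized contrast loses at month 12 is numbers and the ages outside 12–23 months.

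**No age pattern is given.** A reader might infer that the indicator will rise from age alone. That requires diversity to be higher at 12–23 than at 6–11 months, and no section gives diversity by age. Only a possible change of unknown size and sign can be claimed.

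**Other diet measures exist.** Section 5.2 scores diversity at 24–36 months, though under the baseline evaluations and not as a Table 2 outcome. Table 2 also lists minimum meal frequency and consumption of foods rich in iron and vitamin A, neither with a stated window. The diet step of hypothesis 1 therefore does not rest on this indicator alone.

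**The follow-ups may admit new children.** Section 4 says "Those educational interventions will be intercalated with cross-sectional evaluations", which could suggest fresh samples that refill the younger ages. No section provides for new entrants, and Sections 2.3 and 3.6 point the other way.

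**This is analysis-plan detail.** Age adjustment alone would be. But the window, the closed cohort and the before/after comparison are all fixed in this document, and it is their combination that fails.

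**Conclusion.** The point holds for one comparison: the change from baseline to month 12 within each sample. That change sets ages 6–23 against ages 12–23 months and can come from age alone, by about one third of any prevalence gap between the older and younger band. The empty 6–11 month band at month 12 follows directly from closed entry. The share scored at month 12, about a quarter, rests on an assumed age distribution (21–30% for entry at 0–47 months; 28–39% if entry stops near 36 months).

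The between-arm contrast is unbiased in this respect, the month-6 comparison keeps the baseline age mix under even ages, and the primary outcomes are not affected. This is an inexpensive correction to a secondary behavioural outcome whose stated comparison could mislead.

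**What to change.** 1. Rest the conclusion on the difference between arms at each follow-up among children in the 6–23 month window, adjusted for age. State that at month 12 this covers ages 12–23 months only.
2. Make the baseline-to-month-12 comparison only within 12–23 months. If minimum meal frequency uses the same window, treat it the same way.
3. Optionally, report a food-group diversity score from the 24-hour recall for every child aged 6 months or more, as a supplementary measure labelled non-standard above 23 months. The score and cut-off would have to be defined: the seven food groups in Section 3.7 are listed for developing recipes, not for scoring. Replacing the published indicator with this score is not needed.

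**Cost.** Items 1 and 2 change wording only. Item 2 reduces the baseline group from 18/48 to 12/48 of the cohort under even ages. The two groups then share no child (entrants aged 12–23 months against entrants aged 0–11 months), so it compares prevalence at the same ages, not change within a child, and it remains uncontrolled.

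Item 3 needs extra coding of recalls, which the under-5 tool and the repeated baseline design should supply. Its gain in precision should not be overstated. Using all children instead of a quarter halves only the within-hamlet standard error, √(12/48) = 0.5; variation between hamlets is unchanged. Assuming 100 children per hamlet and an intracluster correlation ρ, the ratio of total standard errors is √{[ρ + (1 − ρ)/100] / [ρ + (1 − ρ)/25]}. That is about 0.71, 0.82 and 0.90 for ρ = 0.02, 0.05 and 0.10.
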